## Abstract

**Background:**

Seven years of age is a milestone for learning basic knowledge that is strongly related to attention abilities such as Alerting, Orienting, and Inhibition function, allowing for appropriate adaptation to primary school. These attention abilities are also influenced by gestational age at birth in a complex manner, indicating an area of weakness in prematurely born children. Furthermore, recent studies suggest that allowing children to have freedom of movement during learning may improve their attention level and school performance. The purpose of the present study is to determine the influence of mobility on the attentional components that may impact learning abilities in children aged 7-years who were born at term and prematurely.

**Methods:**

This prospective, randomized, controlled trial will focus on psychometric testing of attentional abilities assessed with the Attention Network Test for Child (Child ANT) and involves a mixed measurement design. Forty-eight children aged 7-years, half of whom were premature at birth and in their expected grade without learning difficulties will be included after parental consent. They will be equipped with a head-mounted display in which the Child ANT will be presented. The association of different flankers and pre-cues will allow the measurement of the development level of Alerting, Orienting, and Inhibition function. The task will be composed of one experimental block of trials randomly performed per posture: seated, standing, or free.

**Discussion:**

This study will assess the contribution of mobility in specific attentional contexts that are usually present during fundamental learning in children. New pedagogical formats of teaching could consider these findings, and new pedagogical tools enabling free spontaneous child mobility might be designed. Moreover, a small percentage of children integrating into the educational system are born prematurely. These children, often considered immature and hyperactive, could benefit from educational innovations that enhance their attention abilities, thereby improving their adaptation to primary school.

**Trial registration:**

This trial is registered at ClinicalTrials.gov (NCT03125447).

## Background

Five to 7-years of age is a milestone in children’s development. At this age, they begin school and acquire the basics of fundamental learning such as reading, writing, and calculating. In a general way, these lessons are strongly related to attentional abilities and executive functions such as working memory and inhibitory control in children [1–8].

Since 1990, Posner’s work highlighted three different attentional networks that are thought to relate to the activation of different brain areas [9]. These cerebral networks are related to three components of attention: sustained attention or alerting (maintaining vigilance abilities), selective attention or orienting (ability to shift the attention), and inhibition function (ability to focus on one feature of a stimulus and ignore other interfering features). Fan et al. [10] developed an integrated Attention Network Test (ANT) based on a flanker task [11] in order to independently measure the efficiency of these three networks. This test was validated in adults, where alerting was induced by warning signals given prior to a target event, orienting facilitated by explicit spatial cues prior to a target event, and inhibition function evaluated by introducing incongruent flankers around the target. The adaptation of this test for children born at term at the ages of 4 to 10-years [12] showed an independence in the development of these three attentional systems. Alerting and orienting components may mature at up to 6-years of age then stabilize, while the inhibition function may improve up to the age of 7-years then remain stable after this age [12].

Little research has assessed the three attention components in children born prematurely. Studies suggest that prematurity may induce delays in maturation for the three attentional networks throughout the preschool years rather than lead to a persistent impairment [13, 14]. These attention components are influenced by age at assessment and gestational age at birth in a complex manner, indicating an area of weakness in children born prematurely [13]. On one hand, the risk for deficits in these attention components increases with decreasing gestational age. On the other hand, the development of these attention components might follow different developmental trajectories in children who were born preterm. For alerting, studies did not show any difference between children born at term versus those born preterm at the age of about 8-years [15, 16]. For orienting, the adult level may be reached at 8-years of age in children born prematurely [15]. A developmental delay of about one year has been observed between children born at term versus those born preterm [17–20]. Finally, data suggest that the inhibition function is still affected by prematurity at the age of 7-years [15–17] and up to 11-years of age in some children [21]. However, many different experimental assessments have been used to study the inhibition function (Tapping Test, Go No-Go Test, Stroop Color World test, Continuous Performance Test, Test Everyday Attention for Children, etc), which have failed to determine consensual and accurate developmental delays for this attentional component.

In general, the attention level of children is considered to decrease when they are moving. The poor attentional performance in those born prematurely as compared to children born at term is also attributed to an impulsivity [16]. Moreover, the urge for mobility is frequently observed in school age children and is often described as “hyperactivity” [22]. However, this is a loaded concept because it implies an attention deficit hyperactivity disorder (ADHD). This concept is one of the most extensively studied childhood psychiatric disorders and has a precise definition [23–25]. The core of ADHD-hyperactive symptoms are poor sustained attention, deficient impulse control (impulsivity), and excessive activity level [24, 26–29]. Thus, this qualification of “hyperactive” is excessive due to the absence of primary attention problems in many of these children, raising the fundamental question of the role of their apparent excessive mobility.

Extensive neuroimaging data highlight the interconnection between cognitive capacities and the sensorimotor state [30]. Human posture and/or mobility governs both neurophysiological arousal [31–33] and cognitive performance [34–38]. In healthy adults, Barra et al. [39] showed that increased body swaying related to imposed postures improved the alerting performance without modulating the orienting and inhibition function. Therefore, contrary to common thinking, mobility does not always seem to be a source of distraction leading to a lack of concentration. For instance, Janssen et al. [40] showed that the implementation of a moderate intensity physical activity break during the school day enhances attention levels, thereby improving school performance. Beyond this exercise-facilitated cognition, several studies suggest that children working in classrooms equipped with desks that allow standing and movement during class time led to significant improvement in their attention, executive control, and working memory [41–44].

### Aim of the study

The purpose of the present study is to determine the influence of mobility on the attention components that may impact learning in healthy children aged 7-years born at term or prematurely. We hypothesize that the absence of mobility constraints may improve alerting performance by increasing arousal in children born at term, without influencing orienting or inhibition function. We also speculate that considering mobility in children born prematurely might help improve some of their attention abilities.

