### Statistical analyses

To determine the number of children to include, we relied upon Rueda et al. [12], showing a global sitting performance of an overall RT of 931 ± 42 ms in 6-years-old children born at term and 833 ± 123 ms in 7-years-old children born at term. Because children born prematurely are usually considered to have about a 1-year delay for learning abilities, we calculated that to demonstrate a catch-up related to the mobility condition, sitting being the reference, for each attention component, with an alpha risk of 0.00625 (Bonferroni correction for the number of tests) and a power of 0.80, 24 children would be needed in each group (Power and Precision™ V4, Biostat Inc., Englewood, NJ, USA 2001).

Thus, we will first compare the overall RT of the children born at term versus those born prematurely. Then, we will compare separately the mean scores (± standard deviation) obtained for each of the attention components. After having verified the required assumptions about data distributions (normality of attentional scores, homoscedasticity and sphericity), the level of each attention component will be analyzed by the means of three mixed analyses of variance, with position condition (seated, standing, free) as a within-subject factor and gestational age (children born preterm vs. children born at term) as a between-subject factor. For all analyses, post hoc tests will be conducted using Tukey’s honestly significant difference method when needed.

To evaluate the subjective arousal level of children between the positions, the Friedman test will be performed on each score on the Self-Assessment Manikin scale with position (seated, upright, and free) as a within-subject factor.

The statistical thresholds for significance will be set to 0.05 for the remaining analyses.

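### The hypothesis that mobility does not influence orienting or inhibition in term-born children has no matching analysis: separate difference tests per component can show neither absence of an effect nor an alerting-specific one

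*Protocol article*

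**What the plan says.** Under Aim of the study, the protocol article states a hypothesis in two parts: removing mobility constraints may raise alerting performance in term-born children "without influencing orienting or inhibition function". The second part predicts no effect on two of the three components, and it is stated for term-born children only. For preterm children the article offers only a looser speculation that some abilities may improve.

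Under Statistical analyses, "the level of each attention component will be analyzed by the means of three mixed analyses of variance", with position (seated, standing, free) as the within-child factor and preterm versus term birth as the between-child factor. After that, "post hoc tests will be conducted using Tukey’s honestly significant difference method when needed". The sample size is set "to demonstrate a catch-up related to the mobility condition, sitting being the reference, for each attention component", at an alpha of 0.00625 with Bonferroni named as the reason. The inputs are overall reaction times of "931 ± 42 ms in 6-years-old children born at term and 833 ± 123 ms in 7-years-old children born at term", and the result is "a power of 0.80, 24 children would be needed in each group" (power first, then number). The section ends by setting 0.05 for the remaining analyses. It gives no margin, smallest effect of interest or confidence-interval criterion for orienting or inhibition, and no comparison of one component's change with another's.

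**The concern.** A test for a difference can reject no effect but cannot support it. The stated plan therefore offers the no-influence part of the hypothesis only one kind of support, a non-significant result, and that result becomes more likely as the data become noisier.

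A second gap follows from analysing each component in its own ANOVA. A significant result for alerting beside a non-significant one for inhibition does not show that the two effects differ; the estimates could be nearly equal.

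What is at stake is the practical message. The Discussion looks ahead to classroom formats that allow movement. A real cost or benefit of free mobility for inhibition or orienting could go undetected, and the results would not show whether it was absent or merely missed.

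**Working it through.** **1. The plan's own figure.** The inputs are the two overall reaction times in Statistical analyses.
- Difference: 931 − 833 = 98 ms.
- Pooled SD: √((42² + 123²)/2) = 91.9 ms.
- Normal approximation, two-sided alpha 0.00625, power 0.80: n = 2 × (91.9/98)² × (2.734 + 0.842)² = 22.5, so 23 per group. The exact t calculation gives 25, with power 0.791 at 24.

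The stated 24 per group is thus reproduced, as a between-group difference in overall reaction time. It says nothing about the precision of a within-child change in orienting or inhibition.

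**2. What each score rests on.** Each position has 48 trials over 4 cue conditions and 3 flanker conditions, that is 12 per cue condition and 16 per flanker condition. Orienting is a difference of two medians, each from at most 12 correct trials. Inhibition is a difference of two medians, each from at most 16. The position effect is then a difference of such differences.

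**3. Chance of missing a real change.** The article gives no SD for the free-minus-seated change and no effect of interest. Assumed here: change SD of 50, 75 or 100 ms, and a true change of 30 ms (0.6, 0.4 or 0.3 SD). The calculation is a two-sided paired t test with noncentrality 30 × √n / SD. For n = 24 this is 2.94, 1.96 or 1.47; for n = 48 it is 4.16, 2.77 or 2.08.

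| Children | Alpha | Missed, SD 50 | SD 75 | SD 100 |
|---|---|---|---|---|
| 24 term | 0.05 | 20% | 53% | 71% |
| 24 term | 0.00625 | 51% | 82% | 92% |
| 48, common effect | 0.05 | 2% | 23% | 47% |
| 48, common effect | 0.00625 | 11% | 53% | 77% |

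The paired test stands in for the planned ANOVA. As a check, a three-position F test in 24 children at 0.05, sphericity assumed and one position shifted, has power 49% at 0.4 SD and 29% at 0.3 SD. It misses 51% and 71%, close to the 53% and 71% above.

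Both alphas are shown because the article gives 0.00625 only in the sample-size sentence and 0.05 for the remaining analyses. Which applies to the component contrasts is unclear.

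**4. What an interval would show.** The 90% half-width is t(0.95, 23) × SD/√24 = 1.714 × SD/4.899 = 0.35 SD, that is 17.5, 26.2 or 35.0 ms. The interval can lie within ± a margin only if its half-width is below that margin.

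**5. Chance of showing no influence when it is true.** With two one-sided 5% tests, 24 children and a true change of zero, simulated power is about 2% at a margin of 0.3 SD, 22% at 0.4, 54% at 0.5 and 77% at 0.6. For a margin of 30 ms, used only as an illustration, that is 77%, 22% or 2% for SDs of 50, 75 or 100 ms. Reaching 80% would take about 26 children at 0.6 SD, 36 at 0.5 and 96 at 0.3.

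**The case against.** The strongest reply is that the article never says how a non-significant orienting or inhibition result will be read. That stands. A reader might infer that non-significance will be taken as confirmation, but no section states such a rule, and the Discussion does not interpret a null component. The point is that nothing planned can support this part of the hypothesis, not that a wrong rule has been written down.

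A second reply is that the clause is a hedged expectation, that the declared purpose is the open one of determining the influence of mobility, and that the trial is sized for something else. This lowers the weight of the point. It does not remove it, because the article itself fixes both the hypothesis and the analysis, and the two do not match. That is not a detail left to a fuller document.

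Third, the 0.00625 rates for 24 children are the pessimistic corner. That also stands. The position main effect uses all 48 children and misses much less if the effect is common to both groups. The hypothesis, however, is about term-born children, and at SDs of 75 or 100 ms the common-effect miss rates at 0.05 are still 23% and 47%.

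A reader might also extend the argument to catch-up, expecting it to be read from a non-significant term-preterm gap in the free position. The article does not support this. It frames catch-up as related to the mobility condition with sitting as the reference, which points to an improvement from seated, and it nowhere defines catch-up as a null gap. Nor is the ANOVA a superiority test in the strict sense; it is an omnibus test for any difference.

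**Conclusion.** The point holds in limited form. The no-influence part of the hypothesis has no analysis that could support it, and no planned contrast shows that the alerting change differs from the other two. This mismatch is in the text and depends on no assumption.

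Its size does depend on assumptions. For a 30 ms change and change SDs of 50 to 100 ms, neither of which is in the article, the chance of missing it runs from 20% to 71% with 24 term children at 0.05, and from 51% to 92% at 0.00625. With an effect common to all 48 children it runs from 2% to 47% and from 11% to 77%. At the low end of the SD range the pooled analysis at 0.05 would rarely miss such a change; at the high end a non-significant result says little under either threshold. The matter should be settled before the data are analysed, but it does not undermine the trial's other comparisons.

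**What to change.** 1. Report the free-minus-seated change in orienting and in inhibition for term children with its confidence interval, and draw no conclusion of absence from p > 0.05. Claim no influence only if the 90% interval lies within ± a margin in ms that is stated and justified before data review. Otherwise report the result as inconclusive.
2. Base any claim that the effect is specific to alerting on a direct contrast of the alerting change against the orienting and inhibition changes, that is a component-by-position interaction in the term group.
3. State which threshold, 0.00625 or 0.05, applies to the component contrasts.

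If no margin can be justified, the alternative is to reword the hypothesis so that it asserts no absence of effect, and to report the intervals.

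The cost is one added contrast on data already collected and some wording. The trade-off is that 24 term children are likely to give an inconclusive verdict for orienting and inhibition unless the change SD is near the low end of the assumed range or the margin is wide.

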## Methods and design

This prospective, randomized, controlled trial will focus on psychometric testing of the attention components and will involve a mixed measurement design. The study will take place in the Maternité Régionale of CHRU Nancy. It will be conducted in accordance with the Declaration of Helsinki. It was approved by the Comité de Protection des Personnes Sud-Est III Ethics Committee (2017–010 B) and registered in the clinicaltrial.gov registry (NCT 03125447). Because the participants will be children, the signed consent of their parents will be requested after they have received written information related to the study. The children will also be asked for their oral consent. Data collected will be analyzed anonymously.

### Inclusion and exclusion criteria

Children aged 7-years will be included in the study. Half will be children who were born prematurely and the other half will be children born at term. For the preterm group, children were born prematurely at or before 34 weeks gestation. They were born and cared for at our level III institution and involved in our routine follow-up program. At the time of the 7 years follow-up visit parents and child will be informed about the study and asked for participation. When they agree to participate an appointment will be taken for the study. For the term group, the children will be recruited using an information leaflet displayed at Lorraine University.

All children will have a clinical examination performed by trained pediatricians. General information on children’s health, socio-demographic data, behavioral problems, vision screening at the time of the test as well as perinatal information will be recorded. These features will be taken into account as potential confounding factors. All children with visual, cognitive, or motor disabilities that would prevent the realization of the test will be excluded. Also, infants with ADHD-inattentive problems will not be part of this study.

### Materials

The Child ANT [12] will be generated by the software, E-Prime (version 3.0 professional; Psychological Software Tools®, Sharpsburg PA, USA) and presented through a head-mounted display (Wear Video Headphones, The Way In®, Vuzix Corporation, New York, USA).

### Design and setting of the study

The head-mounted display will be used to keep the distance between the eyes and the visual stimuli constant across 3 experimental conditions (seated, standing, and free position). The visual target stimulus consists of a yellow fish placed in the center of the visual blue background that is oriented toward the left or right side (Fig.1). This target will be presented either above or below a fixed cross and with or without flanker stimuli. The target will appear either alone (neutral condition) or in the center of a horizontal row of five yellow flanking fishes who will be oriented in the same direction (congruent condition) or in the opposite direction (incongruent condition). Children will be instructed to identify, as quickly and accurately as possible, the direction of the central fish by pressing the right or the left mouse button whatever the direction of the possible flanking fishes. The children will use their preferred hand. Each fish is subtended 1.6 degrees of visual angle and the contours of adjacent fish are separated by 0.2 degrees. The five fish are subtended a total of 8.8 degrees. The target will be presented about 1 degree above or below fixation.

**Fig. 1 Fig1:**
[figure not shown]
Schematic of the Attention Network Test for Child (Child ANT) adapted from Rueda et al [12]

Each target will be preceded by one of the following four warning cues (asterisk) conditions, as illustrated in Fig. 1: (1) no cue with only the fixation cross displayed; (2) a center cue presented at the location of the fixation cross; (3) a double cue, appearing simultaneously 1 degree above and 1 degree below the fixation cross then the target appears at the level of only one of these two cues; or (4) a spatial cue, appearing 1 degree above or 1 degree below the fixation cross, then the target appears at the location of the cue. Each trial will begin with a fixation period of random duration (400–1600 ms). After that fixation period, the warning cue will be presented for 100 ms and will be followed by another fixation period of 400 ms. subsequently, the target and flankers will appear simultaneously. They will be presented until the child responds. The maximal response time allowed will be 2500 ms. After the response, the target and flankers will disappear, and there will be a last fixation period of 3500 ms minus the response time (RT). Then, the next trial can begin.

To test the influence of mobility on the level of the three components of attention, we will ask the children to complete the experimental task in three random positions: (a) in a fixed seated position corresponding to a posture with very low mobility similar to the demand of sitting in a school environment; (b) standing in an upright position corresponding to the human’s reference posture, requiring real balance control due to the natural body sway; (c) in a free position where the children will be able to move and change their position whenever and as often as they want.

To check the children’s understanding of ANT, a 12-trial practice block, lasting less than 2 min, will be executed in the seated position. The children will receive feedback on their success. After this practice block, they will execute 48 trials in each position (with a 1-min 30-s break after 24 trials): 4 cue conditions × 2 target locations (up, down) × 2 target directions (left, right) × 3 flanker conditions (neutral, congruent, incongruent). The order of the trials will be randomized. Overall, each experimental block will last less than 3 min. Between each experimental block, the children will have a 3-min break. During these breaks, they will rate the subjective dimension of their arousal based on the adapted Self-Assessment Manikin scale [45]. They will point to one of five figures on a teddy bears’ scale (Fig.2), or between any two figures, which results in a 9-point rating scale. Overall, the experiment will last about 30 min.

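### Position order is random with no stated balancing and block number is absent from the ANOVA, so any drift in the attention scores costs precision; the stated block length also conflicts with the trial timings

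*Protocol article*

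**What the plan says.** Under Design and setting of the study, the order of the positions is covered in one phrase: "we will ask the children to complete the experimental task in three random positions". The Methods part of the abstract adds "one experimental block of trials randomly performed per posture: seated, standing, or free". Neither place mentions counterbalancing, a Latin square, or separate order lists for the preterm and term groups.

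The analysis, by contrast, is written out. Under Statistical analyses each attention component gets a mixed ANOVA "with position condition (seated, standing, free) as a within-subject factor" and "gestational age (children born preterm vs. children born at term) as a between-subject factor". No other factor is named. The sample size statement is that "24 children would be needed in each group", "with an alpha risk of 0.00625 (Bonferroni correction for the number of tests) and a power of 0.80".

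Data acquisition defines each attention score as a difference between two median reaction times obtained in the same position.

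On timing, Design and setting of the study gives the duration of each part of a trial, 48 trials per position, a 90-second pause after 24 trials and a 3-minute break between blocks. It then states: "Overall, each experimental block will last less than 3 min".

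**The concern.** This is a three-period within-child comparison in 7-year-olds, on outcomes that include vigilance. Practice or fatigue could change a child's alerting, orienting or inhibition score from the first block to the third. Position and block number vary together within each child. If block number is not in the model, that change is counted as unexplained variation in the contrasts the trial is about: the position effect and the group-by-position (catch-up) effect. If the orders are also not balanced, the position means and the two groups can differ by chance in how late each position was done. With 24 children per group and a Bonferroni-reduced alpha in the sample size statement, there is little precision to spare.

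The stated block length bears on this because it understates how long the children are on task.

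**Working it through.** **1. Block length from the protocol's own timings**

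Inputs (Design and setting of the study): first fixation 0.4 to 1.6 s, cue 0.1 s, second fixation 0.4 s. The last fixation is 3.5 s minus the response time, so response plus last fixation is always 3.5 s.

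- Shortest trial: 0.4 + 0.1 + 0.4 + 3.5 = 4.4 s. Longest: 1.6 + 0.1 + 0.4 + 3.5 = 5.6 s. Mean: 5.0 s, if the first fixation averages its mid-range of 1.0 s.
- 48 trials: 48 × 4.4 = 211 s (3.5 min) to 48 × 5.6 = 269 s (4.5 min); mean 48 × 5.0 = 240 s (4.0 min).
- With the pause: 240 + 90 = 330 s = 5.5 min.
- To stay under three minutes a trial would have to take less than 180/48 = 3.75 s, below the 4.4 s minimum. A half-block of 24 trials would fit (106 to 134 s), but the abstract defines one block per posture.
- The third block starts 2 × 5.5 + 2 × 3 = 17 min after the first. The whole session is 12 × 5.0 s of practice (1 min) + 3 × 5.5 + 2 × 3 = 23.5 min, compatible with the stated half hour or so.

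**2. The stated sample size**

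Difference 931 − 833 = 98 ms; pooled SD √((42² + 123²)/2) = 91.9 ms; alpha 0.00625 (= 0.05/8), taken as two-sided because the protocol does not say; power 0.80. This gives 23 per group by the normal approximation and 25 by the noncentral t. The stated 24 is reproduced and is not in question here. It divides exactly: 24/6 = 4 children per order in each group.

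**3. Chance imbalance, if the order is unrestricted**

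This is an assumption; the article says only that order is random. For two positions, the difference in block number is ±1 with probability 2/3 and ±2 with probability 1/3, so its variance is 2/3 × 1 + 1/3 × 4 = 2.

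- SD of the mean difference within a group of 24: √(2/24) = 0.29 blocks.
- SD of the preterm-minus-term difference: √(2/24 + 2/24) = 0.41 blocks.
- Exact 4-per-order balance in one group: 24!/(4!)⁶/6²⁴ = 0.0007.

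The mean of each imbalance is zero.

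**4. Effect on the planned ANOVA**

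Assumptions, none from the protocol: a linear step of d within-child SD per block in the attention score itself, independent within-child errors, nominal 5% tests, and a group-by-position effect of 0.9 SD in the free position. Without a period term the error variance becomes 1 + d², and the SD of the catch-up contrast (free minus seated, preterm minus term) is √((2 + 2d²) × 2/24). Simulation (20,000 runs; 1,500 with period in the model) gave:

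| d | Contrast SD, formula | Contrast SD, simulated | Power, random order, no period term | Type I error / power, balanced, no period term | Power, period term (random / balanced) |
|---|---|---|---|---|---|
| 0 | 0.41 | 0.41 | 0.60 | – | – |
| 0.25 | 0.42 | 0.42 | 0.58 | 0.041 / 0.57 | 0.61 / 0.60 |
| 0.5 | 0.46 | 0.46 | 0.51 | 0.023 / 0.48 | 0.58 / 0.60 |
| 1.0 | 0.58 | 0.58 | 0.34 | 0.002 / 0.21 | 0.60 / 0.61 |

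The Monte Carlo standard error in the last column is about √(0.6 × 0.4/1,500) = 0.013, so its entries do not differ meaningfully.

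With random order and no period term, average bias was −0.007 to +0.009 SD. Type I error was 0.049 to 0.054 for position and 0.050 to 0.053 for group-by-position, including when the drift differed between groups.

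The loss can also be read as sample size: keeping the no-drift precision would take 24 × (1 + d²) children per group, that is 25.5, 30 and 48 for d = 0.25, 0.5 and 1.0.

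**The case against.** Four points against the concern deserve weight.

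- **Bias.** A reader might infer that practice and fatigue bias the position and catch-up effects. The documents do not support that. Order is random, so the drift averages to zero in every contrast and the planned tests keep their level. The chance imbalance in step 3 and the larger error variance in step 4 are one variance described in two ways, not two harms.
- **Simple randomisation.** A reader might also infer that no restriction was used. The article says only random, and a balanced list could sit in the full protocol. This stands, so step 3 is conditional. It does not rescue the analysis: with a balanced list and no period term, the drift still inflates the error and the test becomes conservative.
- **The outcome.** Each score is a difference within a position, so a uniform slowing or speeding cancels. Only drift in the cue or flanker effect counts. This stands. No size for that drift is given, and at a step of 0.25 SD the loss is small (0.60 to 0.58).
- **Block length.** The discrepancy alters no analysis, the session total still fits, and it does not show that drift exists. This also stands, so it is a secondary correction. The arithmetic itself needs no assumption beyond the protocol's timings.

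The practice block is always done seated. Neither balancing nor a period term addresses that.

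**Conclusion.** The point holds as one of precision, not validity. The protocol specifies the ANOVA factors and leaves out block number, states no balancing of order, and has a group size that divides exactly over the six orders. If the attention scores drift over the session, group-by-position power falls by an amount that depends on the drift: negligible at 0.25 SD per block, 0.60 to 0.51 at 0.5 SD, and 0.60 to 0.34 at 1.0 SD. These figures rest on assumed steps, an assumed effect of 0.9 SD and a 5% level; at the alpha of 0.00625 used for sample size, every power would be lower. If there is no such drift, nothing is lost. The stated sample size is unaffected.

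The block-length statement is contradicted by the protocol's own trial timings whatever the drift.

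**What to change.** 1. Prepare an order list for each group in which each of the six orders of seated, standing and free is used four times (6 × 4 = 24), separately for preterm and term children.
2. Analyse each attention score with a linear mixed model with a random child effect and with position, group, position-by-group and block number (1 to 3, as a factor). The Tukey comparisons can be made on the model's position means.
3. Do both. The period term recovers the precision; balancing removes chance differences in block number between positions and groups. Balancing without the period term makes the test conservative.
4. Correct the block duration to about 4 min of trials (3.5 to 4.5), or about 5.5 min with the pause.

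The cost is an order list per group, two model degrees of freedom, replacement of the classical repeated-measures ANOVA, which cannot simply take a factor that changes within child alongside position, and one corrected sentence. No additional children or visits are needed.
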